### Statistics

#### Expected sample size

We based our sample size calculations on the assumption that the pessary reduces the primary outcome (preterm birth <32 weeks) from 40% in the control group to 26% in the pessary group [18]. With a study power of 80% and an alpha error of 5%, (assuming an effect size of 0.5 (moderate) and expecting a potential drop out rate of 10%), the required sample size has been estimated to be 352 patients, 176 cases in each arm of the study. We will perform 2 interim analyses, so the *p*-value would be set at 0.045 (O’Brien-Fleming rule) [23] instead of 0.05 and we would therefore need to recruit 182 patients in each arm.

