#### Data analysis

A descriptive analysis by preterm birth will be carried out calculating means and medians for quantitative variables and proportions for categorical variables. T-test or Mann-Whitney test and Pearson Chi-squared or Fisher test will be used for comparing among exposure and outcomes groups per pregnancy. A multivariate logistic regression will be fitted to control for possible confounders. Relative risks and 95% confidence interval will be calculated for the outcomes.

For fetal and neonatal outcomes, multilevel models will be used to analyse continuous outcomes and generalized estimating equations will be used to assess categorical outcomes to adjust for the clustering of twins in mothers. A secondary analysis of length of gestation after fetoscopy will be plotted on a staggered-entry Kaplan-Meier curve where gestational age at birth (in days) will be the final event. Elective A Mantel-Cox test will be performed to test statistically for significant differences in the time interval between fetoscopy and birth. All analyses will be carried out with SPSS® 19.0 statistical package (IBM Company SPSS Inc. Headquarters, Chicago, Illinois. USA). Statistical significance will be accepted in all cases with a *p* < 0.05.

We do not expect to have lost data because this study has a short follow-up time. We will also perform a per-protocol analysis.

We also intend to perform a subgroup analysis according the cervical length: over 25 mm, 15 to 25 mm and less than 15 mm. We decided to perform the subgroup analysis with these cut-off lengths because 25 mm is around the 5th centile for cervical length for twins less than 22 weeks’ gestation [24] and some groups perform cervical cerclage in TTTS patients with CL below 15 mm [13].

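### The protocol gives two significance levels for the final primary test, 0.045 and 0.05, so a p-value from 0.045 up to 0.05 has no defined outcome

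*Protocol article*

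**What the plan says.** Three neighbouring subsections under Statistics in the protocol article bear on the final threshold.

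- **Expected sample size.** The trial is first sized at 5% alpha and 80% power, giving 176 per arm. The level is then changed: "We will perform 2 interim analyses, so the *p*-value would be set at 0.045" under the O'Brien-Fleming rule, "instead of 0.05 and we would therefore need to recruit 182 patients in each arm".
- **Data analysis.** After the list of tests and the software, the section closes the matter with "Statistical significance will be accepted in all cases with a" p-value below 0.05. It also states "Relative risks and 95% confidence interval will be calculated for the outcomes". Neither sentence sets the primary outcome apart.
- **Interim analysis.** Efficacy boundaries are given for 100 patients (p below 0.0001) and 200 patients (p below 0.004). No level is given for the final analysis.

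**The concern.** The first level is expressly a replacement for 0.05. The second applies 0.05 to everything. Both cannot govern the final test of delivery before 32 weeks, and no sentence says which takes precedence.

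The success criterion of the primary outcome is at stake. If the final p-value falls between the two levels, either conclusion could be defended from the published text, and the choice would be made with the result in view. In addition, the reason for going to 0.045 was to pay for the interim looks. An analyst who follows Data analysis literally gives that payment back.

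**Working it through.** **Inputs.** From Expected sample size: 40% versus 26%, 80% power, levels 0.05 and 0.045, 176 and 182 per arm. From Procedures: 1:1 allocation. From Interim analysis: p below 0.0001 at 100 patients and below 0.004 at 200. Assumptions: two-sided tests (the article does not state sidedness), information proportional to patients enrolled, and no credit for futility stopping. The final analysis is taken at 364 (2 × 182), with 352 (2 × 176, the total in the Abstract) as the alternative.

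**Step 1: reproduce the plan's sample sizes.** The pooled-variance formula without continuity correction is

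n = [z(1−α/2)·√(2·p̄·(1−p̄)) + z(0.80)·√(p1(1−p1) + p2(1−p2))]² / (p1 − p2)²

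with p̄ = 0.33, so 2·p̄·(1−p̄) = 0.4422 and p1(1−p1) + p2(1−p2) = 0.24 + 0.1924 = 0.4324.

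- α = 0.05: (1.9600·0.6650 + 0.8416·0.6576)² / 0.14² = (1.3033 + 0.5534)² / 0.0196 = 175.9, so 176 per arm.
- α = 0.045: (2.0047·0.6650 + 0.8416·0.6576)² / 0.14² = (1.3331 + 0.5534)² / 0.0196 = 181.6, so 182 per arm.

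Both figures reproduce exactly. One-sided versions (139 and 145) and continuity-corrected versions (190 and 196) do not. So 0.045 is a working design input, and the article's sizing is two-sided.

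**Step 2: where 0.045 comes from.** Three equally spaced O'Brien-Fleming looks (100, 200, 300) with overall alpha 0.05 give a final level of 0.0451, which agrees with the stated 0.045.

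**Step 3: overall type I error under each rule.** The probability under the null of crossing any boundary was found by recursive numerical integration over looks at 100, 200 and the final N. The critical values are 3.891, 2.878, and either 1.960 or 2.005.

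| Final level | Final N = 364 | Final N = 352 |
|---|---|---|
| 0.05 (Data analysis) | 0.0512 | 0.0511 |
| 0.045 (Expected sample size) | 0.0463 | 0.0462 |

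The excess over 5% with a final 0.05 is 0.0512 − 0.05 = 0.0012, or about 0.1 percentage point. The disputed zone holds 0.0512 − 0.0463 = 0.0049, or about half a point of probability under the null.

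**Step 4: power at 182 per arm.** Power = Φ[(0.14·√182 − z(1−α/2)·0.6650) / 0.6576], with 0.14·√182 = 1.8887.

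- α = 0.05: Φ(0.890) = 81.3%.
- α = 0.045: Φ(0.845) = 80.1%.

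Under the design alternative, about 1.2 points of success probability lie in the disputed zone.

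**The case against.** **The specific section should govern.** Expected sample size names the interims, the rule and the replacement of 0.05, and the arithmetic confirms that the trial was sized on it. The 0.05 sentence is a general closing line in a section that covers many tests. This is a sensible guess at the intention, and it is the reading that the fix adopts. But the sentence claims to cover every case, the section includes the per-pregnancy comparisons that the primary outcome needs, and no rule of precedence is written.

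**The effect is trivial.** On the error rate this stands: the excess is about 0.1 point, and futility stopping, if followed, can only lower it. It does not answer which threshold applies.

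**An unseen full protocol or analysis plan may fix the final level.** It may. The point here is not missing detail but two incompatible statements in the published text.

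**Stronger readings that a reader might infer.** One is that the trial's error control is seriously compromised; Step 3 shows that it is not. Another takes the wording about an interim after every 100 patients to imply a third look at 300. With an assumed boundary of 0.0194 there, taken from a four-look scheme, a final 0.05 would give 0.0543 (N = 364) or 0.0535 (N = 352). The article does not support this: it states two interim analyses, gives boundaries only at 100 and 200, and contains no 0.0194. Whether a third look is meant is a separate question.

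**Conclusion.** The contradiction is real and should be settled before the final analysis. The primary outcome has two published thresholds, and a final p-value from 0.045 up to 0.05 is positive under one and negative under the other. The main defect is this decision rule. The inflation from using 0.05 is small: about 0.051 overall instead of 5%, while 0.045 keeps it at about 0.046.

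These error rates rest on two-sided tests, the two stated interim boundaries, information proportional to enrolment, and a final N of 364 or 352. The power figures suppose that all 182 per arm are analysed; neither 176 nor 182 contains the 10% dropout allowance that the article mentions, which is a separate matter.

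**What to change.** Replace the Data analysis sentence on significance with one that names a single number, for example: *The primary outcome is significant at the final analysis only if the two-sided p is below 0.045; a nominal 0.05 is used for secondary and exploratory outcomes.*

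The text should not allow 0.045 or a recomputed value. With the stated interim boundaries and a final N of 364, the level that uses exactly 5% is about 0.0488, so such wording would again leave two possible thresholds. Keeping 0.045 is slightly conservative, but it matches the level on which the trial was sized.

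The cost is one sentence and a marginally stricter primary criterion. No extra patients are needed, because 182 per arm already assumes 0.045 and keeps 80.1% power.

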#### Interim analysis

An interim analysis of efficacy and futility will be performed after each 100 patients enrolled in the study using the O’Brien & Fleming rule [23] for efficacy and conditional power calculation to assess futility. The trial will be stopped early if after the first 100 patients the difference has a *p*-value of <0.0001, if after 200 patients the *p*-value reaches a difference of <0.004. The interim analyses as well as the final outcome adjudication will be performed blinded to group assignment.

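### The number of interim looks, the stopping thresholds and the final significance level do not come from one O'Brien-Fleming design and need reconciling

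*Protocol article*

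**What the plan says.** Three sections of the protocol article bear on this point.

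- **Expected sample size.** "We will perform 2 interim analyses". For that reason, and citing the O'Brien-Fleming rule, the final p-value "would be set at 0.045" in place of 0.05, and the size rises from 176 to 182 women per arm (352 to 364 in all).
- **Interim analysis.** "An interim analysis of efficacy and futility will be performed after each 100 patients enrolled in the study", with the O'Brien-Fleming rule for efficacy and conditional power for futility. The efficacy threshold after the first 100 women is a p-"value of <0.0001". After 200 women the p-"value reaches a difference of <0.004". The list ends there.
- **Data analysis.** The general criterion for statistical significance is p < 0.05, with no exception made for the primary outcome.

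**The concern.** A group-sequential plan consists of a number of looks, their timing, a boundary at each look and a final level. These have to come from the same calculation. Here they appear not to.

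- **Number of looks.** One section says two interims. A look at every 100 women in 352 or 364 makes three.
- **Boundary at 300.** If the look at 300 is meant, it has no stated threshold.
- **Source of the thresholds.** 0.0001 and 0.004 look too strict to be the interim bounds of a three-look design that ends at 0.045.
- **Final level.** It is 0.045 in one section and 0.05 in another.

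These figures decide whether an open-label trial stops early and whether its primary result counts as significant. If they are settled only after data have accrued, the error control can be challenged.

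**Working it through.** **Inputs.** Thresholds 0.0001, 0.004 and 0.045; looks at 100, 200 and possibly 300; total 352 (Abstract; Expected sample size) or 364 (2 × 182, Expected sample size); event rates 40% and 26%, power 80%, alpha 5% (Expected sample size). Sidedness is not stated, so two-sided is assumed.

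**Step 1. Reproduce the plan's sample sizes.** Pooled formula per arm:

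n = [z(α/2)·√(2p̄q̄) + z(β)·√(p₁q₁ + p₂q₂)]² / (p₁ − p₂)², with p̄ = 0.33, √(2 × 0.33 × 0.67) = 0.6650 and √(0.24 + 0.1924) = 0.6576.

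- α = 0.05: (1.960 × 0.6650 + 0.8416 × 0.6576)² / 0.0196 = 175.9, so 176. This matches the plan.
- α = 0.045: z = 2.0047, giving 181.6, so 182. This matches the plan.

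The one-sided formula at 0.05 gives 139, so the plan's own figures support a two-sided reading. The step from 176 to 182 rests on the 0.045. Neither figure includes a dropout allowance, which is a separate matter.

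**Step 2. Compute the O'Brien-Fleming bounds.** At information fraction t the critical value is C/√t. C is chosen by recursive numerical integration so that the overall two-sided error is 0.05. The nominal two-sided p-values are:

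| Design | C | Look 1 | Look 2 | Look 3 | Final |
|---|---|---|---|---|---|
| Three equal looks | 2.0040 | 0.0005 | 0.0141 | – | 0.0451 |
| Four equal looks | 2.0243 | 0.00005 | 0.0042 | 0.0194 | 0.0429 |
| 100, 200, 364 | 1.9847 | 0.00015 | 0.0074 | – | 0.0472 |
| 100, 200, 300, 364 | 2.0372 | 0.0001 | 0.0060 | 0.0248 | 0.0416 |
| 100, 200, 352 | 1.9876 | 0.0002 | 0.0084 | – | 0.0469 |
| 100, 200, 300, 352 | 2.0413 | 0.0001 | 0.0068 | 0.0270 | 0.0412 |
| **Stated** | | **0.0001** | **0.004** | **none** | **0.045** |

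Rounded to four and three decimals, 0.0001 and 0.004 are the first two bounds of four equal looks. The 0.045 is the last bound of three equal looks. No row gives the stated set. An O'Brien-Fleming-type spending function does not give it either (100, 200, 364: 0.00018, 0.0081, 0.0468).

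**Step 3. Overall two-sided type I error with 0.0001 at 100 and 0.004 at 200.**

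| Look at 300 | Final level | N = 352 | N = 364 |
|---|---|---|---|
| None | 0.045 | 0.0462 | 0.0463 |
| None | 0.05 | 0.0511 | 0.0512 |
| At 0.0194 | 0.045 | 0.0491 | 0.0498 |
| At 0.0194 | 0.05 | 0.0535 | 0.0543 |
| At 0.05 | 0.045 | 0.0653 | 0.0669 |
| At 0.05 | 0.05 | 0.0685 | 0.0701 |

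With no look at 300, the final level that uses up exactly 0.05 is 0.0489 (N = 352) or 0.0488 (N = 364).

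**The case against.** The best defence is that two interims are plainly intended. The sample size section counts two, and the Interim analysis section lists thresholds for exactly two. Only the phrase about every 100 women is loose. On that reading no look at 300 is left without a boundary, and overall error is 0.046. For 364 women each stated threshold is also stricter than its consistent counterpart: 0.0001 against 0.00015, 0.004 against 0.0074, and 0.045 against 0.047. This defence largely stands. It limits the harm, but it does not make the set coherent: even with two interims, 0.0001 and 0.004 do not belong to a design ending at 0.045.

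A reader might go further and infer that the look at 300 falls to the general p < 0.05 criterion, so that type I error is inflated to 0.065–0.070. The document does not support this. That result needs a third interim that the sample size section does not plan, judged outside the O'Brien-Fleming rule under which the Interim analysis section places its efficacy looks. The 0.05 criterion stands under Data analysis, and the sample size section replaces 0.05 by 0.045 precisely because of the interims.

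It might also be said that an article leaves the full boundary table to the full protocol or analysis plan. That would excuse an omission. It does not excuse stated figures that disagree.

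**Conclusion.** The point holds as an inconsistency to be corrected, not as a demonstrated loss of error control. Three sections give two different interim schedules, thresholds from two different O'Brien-Fleming designs and two different final levels.

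On the best-supported reading the cost is about 0.004 of unspent alpha (0.05 − 0.046). If the general 0.05 criterion were applied at the final analysis, the excess is about 0.001 with two interims, or about 0.004 with a third look at 0.0194. A third look at that level with 0.045 at the end keeps overall error at or just under 0.05.

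It should be fixed, because these are decision figures, but it does not undermine the trial. The conclusion assumes two-sided tests, information proportional to the number of women, and efficacy stopping only, with futility stopping ignored.

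**What to change.** 1. In the Interim analysis section, replace the every-100 schedule by two looks, after 100 and after 200 women.
2. Take all boundaries from one O'Brien-Fleming design at the actual fractions. For 364 women these are two-sided 0.00015, 0.0074 and a final 0.047. Alternatively, keep the stricter 0.0001 and 0.004 and set the final level to about 0.0488.
3. State that final level in the Expected sample size section, and make the Data analysis section use it for the primary outcome.
4. If a look at 300 is intended, say so: correct the count of two interims, give the boundary at 300 and replace the 0.045. For 364 women a consistent set is 0.0001, 0.0060, 0.0248 and 0.0416.

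Steps 1 to 3 cost wording and a short boundary table. The final level is then above 0.045, so 182 per arm remains enough by the plan's own formula. Step 4 would cost a few women: at 0.0416 (z = 2.0375) that formula gives 185.8, so 186 per arm before dropout.

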#### Study calendar

We expect patient recruitment to take approximately 3 years. One more year of duration is estimated for analysis and publication of the results.

## Discussion

Fetoscopic LASER coagulation of the placental anastomoses is the treatment of choice for severe twin-twin transfusion syndrome as this treatment has completely changed the prognosis in terms of survival of these babies. However, the morbidity of these babies is still very high, both at short and long term, mainly due to the high rates of prematurity.

The rate of spontaneous preterm delivery is high, even if the cervical length is in the normal range at the time of the surgery [25]. Almost half of these twins deliver around 32 weeks and most of them are electively delivered around 34 weeks [11, 12], thus we decided that the best cut-off should be “delivery before 32 weeks”, gaining at least two weeks in this group. Likewise, most of the babies are delivered preterm due to complications of the monochorionic placenta such as selective intrauterine growth restriction, twin anemia-policytemia sequence (TAPS) or recurrent TTTS. As this is an intention-to-treat study, the rate of iatrogenic births is expected to be the same in both groups.

In the last decade, some strategies to prevent preterm delivery in twins have been published: bed rest is not useful in twin pregnancies [26], and the use of the cervical cerclage has been questioned [27], despite some groups using it in cases of short cervical length after the fetal surgery [13].

The cervical pessary is a simple and easy-to-use method to prevent preterm birth that has been proven to be effective in singleton pregnancies [20], twins [18] and in the subgroup of monochorionic twins in the ProTwin Trial [22].

As far as we know, there is only one pilot study in this field [21], with favourable results for the pessary. Therefore, a trial that compares the use of the cervical pessary to expectant management in cases of twin-twin transfusion syndrome undergoing fetoscopic LASER coagulation is needed.

## Abbreviations

CL: Cervical length
EC: Ethics Committees
FLC: fetoscopic LASER coagulation
TAPS: twin anemia-policytemia sequence
TTTS: Twin-to-Twin Transfusion Syndrome
